### Pathologic examination

All resected specimens will be sent to a central, dedicated pathologist for assessment of complete histologic eradication at all study hospitals. The pathologist will be a gastrointestinal specialist who will be blinded to the clinical information, including randomization. The diagnosis of adenomatous lesions will be based on the 2010 World Health Organization classification of tumors [24].

### Outcome variables

The primary and secondary outcome measures are shown in Fig. 2. The primary outcome measure is the risk of delayed bleeding within two weeks after polypectomy. Bleeding is defined as any of following:

**Fig. 2 Fig2:**
[figure not shown]
Target lesions are colorectal neoplasms 4–10 mm in size and with flat or sessile morphology. The primary outcome measurement is the risk of delayed bleeding

1. Hemoglobin drops ≥ 2.0 g/dL in comparison with the baseline;

2. Requires blood transfusion;

3. Hematochezia occurs;

4. Requires intervention for hemostasis, including endoscopic hemostasis, transarterial embolization, or surgery.

Secondary outcome measures include the number of hemoclip applications, complete histological and visual confirmation of eradication, histopathology of resected polyps, tissue retrieval rate, procedure time, emergency service visits, and other adverse events such as immediate bleeding during the procedure or perforation (Fig. 2). The study nurses/assistants will contact all patients by phone calls on day 2 and day 14 after the colonoscopy procedure to collect these information. Please see Fig. 3 for the scheme of schedule of enrollment, interventions, and assessments.

**Fig. 3 Fig3:**
[figure not shown]
Schedule of enrollment, interventions, and assessments as per Standard Protocol Items: Recommendations for Interventional trials (SPIRIT)

### Sample size calculation and statistical analysis

This RCT is designed as a two-arm comparison. The risk of delayed bleeding after polypectomy is based on previous publications and is estimated to be 0.6% [25]. The risk of delayed bleeding is assumed to be reduced by 77% in cold snaring polypectomy in comparison with hot snare polypectomy [26]. When the statistical power is set at 80% and the significance level at 0.05, the estimated total sample size is 4258 patients with 2129 in each arm.

The statistical analyses will be performed on an intention-to-treat basis. Values will be expressed as mean ± standard deviation (SD) or median, as appropriate. Comparisons of continuous and categorical data will be made using Student’s *t*-test and the chi-square test, respectively. A *p* value < 0.05 will be considered statistically significant.

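### The 2129 per arm comes from a one-sided 5% calculation, but the planned chi-square test at p < 0.05 is two-sided, so power is about 70%, not 80%.

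*Protocol article*

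**What the plan says.** Everything needed is in the Protocol article, section Sample size calculation and statistical analysis.

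- The delayed-bleeding risk is put at 0.6%, and it is "assumed to be reduced by 77% in cold snaring polypectomy in comparison with hot snare polypectomy".
- The error rates are given as follows: "When the statistical power is set at 80% and the significance level at 0.05". Whether the level is one-sided or two-sided is not stated.
- The result is that "the estimated total sample size is 4258 patients with 2129 in each arm".
- Categorical outcomes, which include the primary outcome, are to be compared with the chi-square test. The criterion is that a p "value < 0.05 will be considered statistically significant".

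The Randomization section gives 1:1 allocation. No section mentions a one-sided test or a directional rejection rule.

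**The concern.** The sample-size sentence and the analysis sentence appear to use different criteria. A chi-square test on a 2×2 table rejects for a difference in either direction, so p < 0.05 is a two-sided 5% rule. If the patient number was worked out with a one-sided 5% level, the trial does not have the stated power for its own primary test.

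This matters more here than in most trials. The Abstract, Background and Discussion all justify the trial by the low power of earlier randomized trials. A non-significant result would be read as coming from a trial with a 20% chance of missing the assumed effect, when that chance is nearer 30%. If the mismatch were noticed only after the data are in, there would also be a temptation to settle it by adopting the one-sided criterion, which relaxes the standard of evidence after the fact.

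**Working it through.** **Inputs** (Sample size calculation and statistical analysis; allocation from Randomization)

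- Hot arm: p1 = 0.006. The 0.6% is read as the hot-snare risk because the reduction is stated relative to hot snaring.
- Cold arm: p2 = 0.006 × (1 − 0.77) = 0.00138.
- Difference: d = 0.00462, so d² = 0.0000213444.
- Mean risk with 1:1 allocation: p̄ = (0.006 + 0.00138)/2 = 0.00369.
- Power 80%: z = 0.8416.

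**Formula** (pooled variance, no continuity correction)

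n per arm = [zα·√(2p̄(1−p̄)) + 0.8416·√(p1(1−p1) + p2(1−p2))]² / d²

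with √(2p̄(1−p̄)) = 0.085748 and √(p1(1−p1) + p2(1−p2)) = 0.085686.

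**Reproducing the plan's figure: one-sided 5%, zα = 1.645**

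(0.141043 + 0.072115)² / 0.0000213444 = 0.0454366 / 0.0000213444 = 2128.7, which rounds up to **2129**. This is an exact match.

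**Same inputs: two-sided 5%, zα = 1.960**

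(0.168064 + 0.072115)² / 0.0000213444 = 0.0576858 / 0.0000213444 = 2702.6, which rounds up to **2703** per arm, 5406 in total.

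Shortfall: 2703 − 2129 = 574 per arm; 574/2129 = 27%.

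**Could another two-sided calculation give 2129?**

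| Method at 0.6% vs 0.138%, 80% power | One-sided 5% | Two-sided 5% |
|---|---|---|
| Pooled | 2129 | 2703 |
| Unpooled | 2127 | 2700 |
| Continuity-corrected | 2544 | 3121 |
| Arcsine | 1896 | 2407 |
| Log relative risk | 2552 | 3239 |

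No two-sided version comes near. Other readings of the inputs do not help. Taking 0.6% as the average of the two arms gives 1306 (one-sided) or 1658 (two-sided), and taking it as the cold-arm risk gives 483 or 613. Rounding the cold-arm risk to 0.1% gives 2189 two-sided, which is still not 2129 and implies an 83% reduction rather than 77%.

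**Power of the planned test at 2129 per arm**

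Normal approximation, two-sided: z = (√2129 × 0.00462 − 1.960 × 0.085748)/0.085686 = (0.213172 − 0.168064)/0.085686 = 0.526, so power = **70.1%**. With 1.645 in place of 1.960 the result is 80.0%.

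Expected events are 2129 × 0.006 = 12.8 and 2129 × 0.00138 = 2.9. With counts this small, exact enumeration over both binomial distributions is a useful check:

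| Two-sided test at 0.05 | Exact power at 2129 per arm |
|---|---|
| Pearson chi-square, uncorrected | 73.0% |
| Chi-square with Yates correction | 63.0% |
| Fisher's exact test | 64.8% |

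The exact power of the uncorrected Pearson test is 79.7% at 2450 per arm, 80.6% at 2500 and 83.9% at 2703.

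**What would restore 80% at 2129 per arm** (two-sided, normal approximation): a true reduction of about 84% from 0.6%, or a hot-arm risk of about 0.76% with the 77% reduction kept.

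**The case against.** The strongest counter-argument is that one-sidedness is inferred. The article gives only "the significance level at 0.05", the hypothesis is directional throughout, and the full protocol and analysis plan are not at hand. The exact match could reflect a deliberate one-sided design that the article failed to label. In that case 80% would be correct, and the defect would be a missing word plus an analysis sentence that applies generically to all categorical outcomes. This stands as a possible account of how the number arose. It does not rescue the text: the article prints the inputs, the resulting number, the test and the threshold, and they disagree. No later document can make 2129 per arm give 80% power for a two-sided test at these rates.

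A second point is partly right. The 2703 and the 574-patient shortfall belong to the normal approximation, the sponsor's type of formula. Judged by exact power, the uncorrected Pearson test reaches 80% somewhere between 2450 and 2500 per arm, a gap of roughly 320 to 370 patients per arm (15–17%). The figure should be labelled accordingly, but the planned number still falls short.

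Third, the choice among Pearson, Yates and Fisher, and any allowance for loss to follow-up, are matters an article may leave to fuller documents. That is fair, and the finding does not depend on them.

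**Conclusion.** The stated 80% power does not hold for the test as written. The 2129 per arm is a one-sided 5% figure. Under the planned two-sided chi-square at 0.05, power is about 70% by the formula that reproduces the plan's number, and 63% to 73% by exact calculation depending on the version of the test. The chance of missing the assumed effect is therefore roughly 27% to 37%, not 20%.

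This rests on reading 0.6% as the hot-arm risk, on taking the 77% reduction at face value, and on complete outcome data. If, as an assumption, 5% of patients had no day-14 outcome, power would be about 68% by the normal approximation and 70% by exact enumeration for the uncorrected Pearson test.

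The validity of the two-sided test and its type I error are not affected. What is wrong is the power claimed for the primary comparison.

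**What to change.** Choose one basis and state it in the sample-size section.

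1. **Preferred: keep the two-sided 0.05 test and correct the power.** For example: with 2129 patients per arm, a two-sided 5% test has about 70% power (normal approximation) to detect 0.6% versus 0.138%; 80% power by the same formula would need 2703 per arm, 5406 in total. This costs one sentence and no extra patients.
2. **Keep 80% power and enlarge the trial** to 5406 patients, which is 1148 more than planned.
3. **If a one-sided 5% test was intended,** say so, justify it, and rewrite the analysis sentence to match before any outcome data are seen. This is a weaker standard of evidence than the current text implies.

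Whichever is chosen, one added line should name the version of the primary test, because the Yates correction or Fisher's test costs a further 8 to 10 points of power. The uncorrected Pearson test fits the sample-size formula best. Its exact size at 2129 per arm is about 4.8% at a common risk of 0.37% and about 5.2% at 0.6%, so it can run slightly above 5%.

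The Trial status section says the trial was still in preparation, so the correction can be made before recruitment.

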### Study patients

Patients scheduled for screening or surveillance colonoscopy will be prospectively screened for eligibility and 4258 patients will be enrolled during the study period. The workflow is shown in Fig. 1. The inclusion criteria are as follows: patients aged > 20 years; have an indication for colonoscopy; and have at least one colorectal polyp of 4–10 mm in diameter. Patients who fulfill at least one of the following exclusion criteria will be considered ineligible for this study: (1) age < 20 years; (2) any contraindication for colonoscopy or polypectomy; (3) pregnancy; or (4) inadequate bowel preparation that could interfere with the procedure or polypectomy. The patients will be enrolled into this trial and provide informed consent at outpatient clinic visiting; they will have enough time to consider whether to participate in this study. The patients’ enrollment will not be the same day of the colonoscopy procedure. In addition, the management of antithrombotic agents for enrolled patients will follow the updated American Society for Gastrointestinal Endoscopy (ASGE) guideline [21]. Patients who fulfill the inclusion criterion will be randomized into either cold or hot snaring polypectomy treatment groups.

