### Randomization

Randomization will be based on the appearance of the target lesions, polyps sized 4–10 mm, present at colonoscopy. Eligible patients will be centrally randomized 1:1 into either cold or hot snaring polypectomy by online software. The online software will be a web-based computer program accessed via an application on a smartphone (Interrand Inc., Ottawa, ON, Canada). Randomization procedures will be conducted by research assistants in the endoscopy units. The patients will be blinded about which treatment group they are randomized into during and after the procedures.

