### Procedures

For both groups, the procedures for bowel preparation and colonoscopy insertion will take place as described in a previous study [22]. Colorectal polyps sized < 4 mm will be removed by forceps biopsy. Lesions sized 4–10 mm will be removed either by hot or cold snaring polypectomy based on the allocation arm. No matter hot or cold snaring polypectomy, saline or adrenaline solution injection to the lesion will not be performed before polypectomy. Lesions sized ≥ 10 mm will be removed by hot snaring polypectomy, endoscopic mucosal resection (EMR), or endoscopic submucosal dissection (ESD) as indicated and based on the feasibility, risk, and patients’ consent. Patients who are allocated to the cold snaring group will receive snaring polypectomy without electrocautery for all target lesions except for lesions > 10 mm, for which hot procedures (polypectomy, EMR, or ESD) will be applied.

Image-enhanced endoscopy with either narrow band imaging or chromoendoscopy with 0.4% indigo carmine spraying will be applied in both arms before polypectomy, to confirm the diagnosis, and after polypectomy, to optically evaluate the complete eradication [23]. The total procedure time, the insertion time, the time to withdrawal, and the time required for polypectomy will be recorded.

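### The plan names a plain chi-square test for all categorical data, which does not fit complete eradication and tissue retrieval if they are analysed per polyp, because patients are randomised

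*Protocol article*

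**What the plan says.** All references are to the protocol article.

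- **Tests** (Sample size calculation and statistical analysis). One sentence covers all outcomes: "Comparisons of continuous and categorical data will be made using" Student's t-test for continuous data and chi-square for categorical data ("test and the chi-square test, respectively"). Analysis is by intention to treat, with significance at p < 0.05. No exception is made for outcomes with several observations per patient.
- **Unit of randomisation** (Randomization): "Eligible patients will be centrally randomized 1:1 into either cold or hot snaring polypectomy by online software".
- **Polyps per patient** (Study patients): a patient must "have at least one colorectal polyp of 4–10 mm in diameter". There is no upper limit and no expected mean.
- **Treatment within a patient** (Procedures): cold-group patients "will receive snaring polypectomy without electrocautery for all target lesions". Lesions of 4–10 mm follow the allocated arm in both groups.
- **Outcomes** (Outcome variables, list of secondary measures): these include "complete histological and visual confirmation of eradication, histopathology of resected polyps, tissue retrieval rate".
- **Level of assessment** (Pathologic examination): "All resected specimens will be sent to a central, dedicated pathologist for assessment of complete histologic eradication".
- **Benchmarks for eradication** (Discussion): these are counted in polyps. One is a trial of 796 polyps with complete resection of 98.2% versus 97.4%. Another is an incomplete resection rate of 6.8% for hot snaring of polyps of 5–9 mm.

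**The concern.** The chi-square test assumes independent observations. Here the technique varies only between patients, while a patient may contribute several polyps that share the same bowel, endoscopist and session. If results within a patient are positively correlated, polyps carry less information than the same number of independent ones. A per-polyp chi-square test then understates the standard error of the difference between arms.

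The Discussion treats complete eradication as the measure of how well the technique works, and the abstract expects to show that cold snaring is effective as well as safe. Eradication is thus the counterweight to the bleeding result. Intervals that are too narrow would let a chance difference in resection or retrieval, in either direction, be reported as significant.

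**Working it through.** **The plan's own figure.** The article states no number for any polyp-level outcome. Its one calculation, 4258 patients (2129 per arm), concerns delayed bleeding, a patient-level outcome. With 0.6% against 0.6% × (1 − 0.77) = 0.138% and 80% power, the usual two-proportion formula (pooled variance, no continuity correction) returns 2129 per arm at a one-sided 5% level. Whether that level is the intended one is a separate question. Clustering of polyps does not enter this calculation.

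**Inputs for the check.** The structure comes from the article: patients are randomised, there are one or more target polyps per patient, and one technique per patient. Two quantities are not in the article and are assumed:

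- *m*, mean target polyps per patient: 1.5, 2 or 3
- ICC, correlation of results within a patient: 0.05 to 0.3

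**Formulas.** With *m* polyps per patient:

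- Design effect: DE = 1 + (*m* − 1) × ICC
- True size of a nominal two-sided 5% test that ignores clustering: 2 × [1 − Φ(1.96 / √DE)]

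**Worked example**, *m* = 3 and ICC = 0.3: DE = 1 + 2 × 0.3 = 1.6; 1.96 / √1.6 = 1.549; size = 2 × [1 − Φ(1.549)] = 12.1%.

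| *m* | ICC 0.05 | ICC 0.1 | ICC 0.2 | ICC 0.3 |
|---|---|---|---|---|
| 1 | 5.0% | 5.0% | 5.0% | 5.0% |
| 1.5 | 5.3% | 5.6% | 6.2% | 6.8% |
| 2 | 5.6% | 6.2% | 7.4% | 8.6% |
| 3 | 6.2% | 7.4% | 9.8% | 12.1% |

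With ICC = 0 every row is 5.0%. Over the grid from *m* = 1.5 to 3, DE runs from 1.025 to 1.6, so correct intervals are wider by a factor of √1.025 = 1.01 to √1.6 = 1.26.

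**Check by simulation.** Trials with no true difference were simulated 4000 times per setting: 2129 patients per arm, 1 + Poisson polyps per patient with means 1.5, 2 and 3, beta-binomial incomplete resection at 7% (close to the cited 6.8%), and the same ICC values.

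- Plain chi-square test: rejected in 4.6% (mean 1.5, ICC 0.05) to 14.7% (mean 3, ICC 0.3) of runs.
- Patient-clustered variance: rejected in 4.2% to 5.5% of runs, that is, about 5%.

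The Monte Carlo margin is about ±0.7 points near 5% (1.96 × √(0.05 × 0.95 / 4000)) and about ±1.1 points near 14.7%. The 4.6% is therefore compatible with 5%.

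The top simulated value exceeds 12.1% because the polyp counts varied. With unequal counts, *m* in the design effect is replaced by E(*m*²)/E(*m*). For 1 + Poisson(2) this is (9 + 2)/3 = 3.67, so DE = 1 + 2.67 × 0.3 = 1.8 and the size is 14.4%. That depends on a further assumption, the spread of polyp counts.

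**The case against.** **The unit is not stated.** The article never says that eradication, retrieval or histopathology will be analysed per polyp. It analyses by intention to treat and counts its sample in patients. If each patient were reduced to one result, the chi-square test would be valid. This stands, and it makes the point conditional. A reader might infer that the plan commits itself to a per-polyp chi-square test; the text does not go that far. It does describe these outcomes at specimen or polyp level, cites per-polyp benchmarks, and defines no patient-level version.

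**This belongs in a document not shown.** An article may leave the handling of correlated data to the full protocol or analysis plan. Silence would be no finding. But the article is not silent: it fixes a test for all categorical data, and that test does not fit outcomes counted per polyp. This objection does not remove the point.

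**The t-test is not at fault here.** A reader might extend the criticism to Student's t-test. The three outcomes named are categorical, so the t-test does not apply to them. The same reasoning would hold only for a continuous measure recorded per polyp.

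**The size is assumed.** This stands. At 1.5 polyps per patient and an ICC of 0.05 the excess is negligible, so a firm statement that the error rate is well above 5% is not supported.

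**Histopathology matters little.** A polyp's histological type is fixed before it is resected, so a comparison between arms is mainly descriptive. This also stands; the practical concern is eradication and retrieval.

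**Conclusion.** The point holds conditionally. The article prescribes the plain chi-square test for all categorical data, although its own description of eradication and retrieval points to the polyp as the unit and its randomisation makes the patient the independent unit. Followed per polyp, the rule gives standard errors that are too small whenever results within a patient are positively correlated.

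The true type I error of a nominal 5% test is then about 5.3–12% for equal polyp counts, with 1.5–3 polyps per patient and an ICC of 0.05–0.3. That range runs from negligible to material: at three polyps and an ICC of 0.2 or more it is 9.8–12.1%. Both inputs are assumptions, and uneven polyp counts can raise the figure further.

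Only secondary outcomes are concerned. A reader might infer that the bleeding comparison or the sample of 4258 is compromised by this. Neither is: delayed bleeding is one result per patient.

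**What to change.** In the analysis section, state the unit of analysis for complete histological eradication, complete visual eradication, tissue retrieval and histopathology. For each, choose one of two routes:

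1. **Per polyp:** replace the plain chi-square test with an analysis clustered by patient, such as logistic GEE, a cluster-robust variance by patient, or a mixed logistic model with a patient random effect.
2. **Per patient:** define one result per patient (for example, all target polyps completely resected, yes or no) and keep the chi-square test.

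For any continuous measure recorded per polyp, replace the t-test in the same way. Keep the chi-square test for delayed bleeding as far as this point is concerned.

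The cost is a sentence or two of text and routine code. No more patients are needed, and the only data requirement is that each polyp record carries its patient identifier. Under route 1, intervals for these outcomes widen by about 1% to 26% over the assumed range with equal polyp counts.

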## Discussion

Cold snaring polypectomy is expected to reduce the risk of delayed bleeding by avoiding thermal injury. However, previous RCTs failed to prove the protective effect of cold snaring polypectomy because of their limited sample sizes. In this study, we will enroll a much larger sample size compared with previous studies in order to demonstrate the benefit of reducing delayed bleeding by cold snaring polypectomy. In addition, another advantage of cold snaring polypectomy is time savings in comparison with hot snaring polypectomy. This has been explored by previous studies and will be also confirmed in this study.

Complete histologically or optically confirmed eradication is an important outcome to evaluate the efficacy of the therapeutic technique. The reported incomplete resection rate following cold snaring polypectomy is 7–21% [13, 27–29] In contrast, following hot snaring polypectomy the incomplete resection rate is 6.8% for polyps sized 5–9 mm [30]. A recent RCT in Japan included 796 polyps sized in the range of 5–9 mm and concluded that the complete resection rate for cold snare polypectomy is not inferior to that for hot snare polypectomy (98.2% vs 97.4%, respectively) [31]. We will compare the complete histologically and visually confirmed eradications between cold and hot snaring polypectomy. This will help to clarify the relative efficacy of cold snaring polypectomy. Moreover, tissue retrieval rates, the frequency of hemoclip application, and any adverse effects will also be evaluated in the study. Thus, this RCT will provide a comprehensive comparison between cold and hot snaring polypectomy.

Diminutive or small colorectal polyps comprise the majority of lesions that should be removed at colonoscopy. Unfortunately, endoscopists use a variety of techniques to remove diminutive or small lesions and practitioners must identify the most cost-effective and safe techniques to treat such lesions. In this study, we will conduct a comprehensive evaluation of cold snaring polypectomy and the results of this RCT will provide a valuable information for future standardization of cold snaring polypectomy for treating diminutive or small lesions.

